**Methods/Design:**

This study includes three of the most deprived electoral wards in Stoke-on-Trent. In each of these areas, environmental factors including proximity of physical activity spaces, greenspace and leisure facilities, neighbourhood connectivity and walkability, land-use-mix and population density, traffic, safety and crime, and food outlets will be mapped using Geographical Information Systems (GIS). A community postal survey of randomly selected addresses assessing environmental characteristics relating to physical activity, perceived health status, social capital, fruit and vegetable consumption and levels of physical activity will be undertaken (baseline and at 2 year follow-up). Based on baseline findings an intervention will be designed and implemented over a 2 year period that includes the following; use of community participatory research to build effective community partnerships; use of partnership consensus to identify, prioritise and design intervention(s) related to specific health disparities; recruitment of local residents to help with the delivery and sustainability of target intervention(s); and the development of local systems for ongoing monitoring and evaluation of the intervention(s).

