### Study population

Our study will include targeted lower level Super Output Area (SOAs), the smallest geographical unit for which census information is available in the UK, in three deprived wards in Stoke-on-Trent, UK (Meir, Burslem South and Bentilee) that are similar with regards to socio-economic status (i.e. in the most deprived 40% of the 2007 Index of Deprivation - (IMD)) and are not undergoing major housing regeneration over the next 3 years. A lower level Super Output Area consists of a population size of ~1,500. These spatial units were chosen because they provide an approximate neighbourhood level of analysis due to their population size and are tied to UK Census data.

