### Proposed sample size

Sample size calculations for the independent survey sample are based on Cohen's arcsine transformation for estimating differences between proportions [15], where;

$$\begin{array}{c} \varphi =2\;\text{arcsine}\left(\sqrt{\text{p}}\right)\\ \text{h}=\left|\varphi_{1}-\varphi_{2}\right| \end{array}$$

P is the proportion and h is the effect size to be detected. The best available estimate of the population proportion currently active at the recommended level was that taken from Active People Survey 2 [16] (sub-group NS-SEC 6-8 i.e. those most closely matching the demographic profile of the target population for this study), which was 7.5%. Based on our previous research [17], we anticipate being able to achieve a 10% increase in this population proportion i.e. 17.5% after the community-led intervention. Using Cohen's arcsine formula this gives a standardised effect size of 0.273. Assuming a false positive error rate of .05, statistical power of .8 and this standardised effect size, we have calculated a required sample size of 283 participants at follow-up. Further, assuming a survey response rate of 10% (expected to be low for this target population) the issued sample size will be 2830 surveys.

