### Phase IV

#### Primary and secondary outcomes

##### Primary outcome measures

The primary outcome measure of effectiveness of this approach will be the change in physical activity in the three areas compared with the other wards in Stoke-on-Trent (using the Active People Survey [16]). The study is designed to detect a 10% increase (intervention areas vs. the rest of Stoke-on-Trent) in the proportion of participants reporting an increase in physical activity, made up of those initially engaging in some activity who increase this to the level recommended to derive health benefit and those initially doing little or no activity who increase to doing some regular activity. Objective measures of physical activity will be used for a random sub-sample of respondents to the community survey using 7-day accelerometry (ActiGraph) as a check on self-reported physical activity measures [26].

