## Discussion

The need for a community-led collaborative approach to combating social inequalities in health has grown out of the recognition that many of the complex determinants of health lie beyond the control of the individual and even of clinical and public health institutions alone. Social factors have a strong influence on health and longevity. Those in deprived areas often lack access to health services, which reduces their likelihood of having disease detected early, live in areas where there is poor access to fresh affordable food and areas to play and participate in physical activities (green space areas run down, vandalised) and often have a number of lifestyle modifiable risk factors (e.g. smoking, sedentary behaviour, high alcohol intake) that compound these health issues. In addition, those living in poor areas are more likely to suffer from depression, stress and poor mental health [31,32].

There is a need to develop evidence-based practice around health interventions that improve public health of communities. Development of an evaluation framework and dissemination of best practice would add considerably to the current evidence-base and offer possibilities for future service innovation across other NHS PCTs.

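### The primary endpoint depends on each area's starting activity mix, so the crude comparison of the wards with the rest of the city can show a difference without any intervention effect

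*Protocol article*

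**What the plan says.** The Primary outcome measures section (Phase IV) sets the contrast: "The study is designed to detect a 10% increase (intervention areas vs. the rest of Stoke-on-Trent"). The quantity compared is a difference "in the proportion of participants reporting an increase in physical activity". That proportion has two parts. The first part is people "made up of those initially engaging in some activity who increase this to the level recommended to derive health benefit". The second part is the group described as "those initially doing little or no activity who increase to doing some regular activity". The section states no exclusion for people who start at the recommended level.

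On how the areas differ:
- The abstract, under Methods/Design, says: "This study includes three of the most deprived electoral wards in Stoke-on-Trent".
- The Study population section describes the wards as "in the most deprived 40% of the 2007 Index of Deprivation". The similarity claimed there is among the three wards, not between the wards and the comparator.
- The Proposed sample size section takes 7.5% as the share active at the recommended level. The figure comes from a socio-economic sub-group described as "those most closely matching the demographic profile of the target population for this study".
- The Discussion says that people in deprived areas "often have a number of lifestyle modifiable risk factors (e.g. smoking, sedentary behaviour, high alcohol intake").

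The Data analysis section names a chi-squared test on activity categories and a multinomial logistic regression giving odds ratios between areas. It mentions no starting category. The only weighting described, in the Community survey section, corrects for selecting one adult per household.

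**The concern.** An endpoint that counts upward moves is a weighted sum of move rates, and the weights are the shares of people in each starting category. People at the top category enter with weight but no possible success. People in the two lower categories enter with rates that need not be equal.

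If two areas start with different mixes, the endpoint differs between them even when residents in the same starting category have exactly the same chance of becoming more active. In a non-randomised comparison of deprived wards with the rest of a city, that difference would be read as an intervention effect. The article plans to use its effect size to design a larger controlled trial, so a composition effect could be carried forward.

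**Working it through.** **Inputs from the article.** Share at the recommended level in the target population: 7.5%. Follow-up sample: 283. Target difference: 10 percentage points. The article gives no figure for this upward-move endpoint that could be reproduced. The 283 was derived for another quantity, the share at the recommended level (7.5% to 17.5%). Those proportions give h = 0.308 rather than the stated 0.273, but that is a separate matter and does not bear on this point.

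**Assumed inputs.** The article gives neither the split of the wards' remaining 92.5%, nor the starting mix in the rest of the city, nor any move rate. All are assumptions below. The wards are taken as 60% little or none, 32.5% some, 7.5% recommended.

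**Formula.** Let r1 be the rate of moving from little or none to some, and r2 the rate from some to recommended, both the same in every area (no intervention effect). Then

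P(counted as increased) = share none × r1 + share some × r2 + share recommended × 0.

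**Main case.** Rest of city 45/40/15, r1 = 25%, r2 = 10%.
- Wards: 0.60 × 0.25 + 0.325 × 0.10 = 0.1825.
- Rest: 0.45 × 0.25 + 0.40 × 0.10 = 0.1525.
- Difference: +3.0 points with no effect.
- With 283 ward respondents and an assumed 800 comparators, SE = √(0.1825 × 0.8175/283 + 0.1525 × 0.8475/800) = 0.0262. Then 0.030/0.0262 is about 1.14, and a nominal 5% two-sided test rejects about 21% of the time.

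**Other assumed cases, wards unchanged.**

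| Rest of city (none/some/rec.) | r1 / r2 | Wards | Rest | Difference (points) |
|---|---|---|---|---|
| 45/35/20 | 30% / 10% | 21.25% | 17.00% | +4.25 |
| 45/40/15 | 25% / 10% | 18.25% | 15.25% | +3.0 |
| 45/35/20 | 10% / 30% | 15.75% | 15.00% | +0.75 |
| 50/40/10 | 20% / 30% | 21.75% | 22.00% | -0.25 |
| 45/45/10 | 20% / 30% | 21.75% | 22.50% | -0.75 |
| 60/32.5/7.5 (same as wards) | any | equal | equal | 0 |

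**Where the difference cancels.** It is zero when r2/r1 = (none in wards − none in rest)/(some in rest − some in wards). For 45/40/15 this is 0.15/0.075 = 2; for 50/40/10 it is 0.10/0.075 = 1.33; for 45/35/20 it is 0.15/0.025 = 6. No single ratio holds across mixes.

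**How much is the ceiling alone.** With one move rate t for everyone below the recommended level, the difference is t × (share recommended in rest − 0.075). At t = 20% this is 0.5, 1.5 and 2.5 points for a comparator with 10%, 15% and 20% already active. In the main case, dropping only those already at the level gives 0.1825/0.925 = 19.7% against 0.1525/0.85 = 17.9%, so +1.8 points remain. The split between the two lower categories therefore matters as well as the ceiling.

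**Conditioning on starting category.** Within little or none, both areas have r1; within some, both have r2. Each stratum difference is 0, so any weighted combination is 0 under this model.

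**The case against.** The strongest objection is that the article fixes none of the quantities that create the bias. Selection was on deprivation, not on activity. The 7.5% comes from a sub-group chosen for its demographic match, and no activity figure is given for any other group or for the rest of Stoke-on-Trent. The article also describes the city as a whole as deprived. This stands. A reader might infer that starting activity differs by design, but that is certain only for deprivation. For activity it is an inference that the sample-size and Discussion sections support and do not establish.

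A reader might also infer that the bias always favours the wards, or that a known part of the 10-point target can be met by composition. The table does not support either reading: the sign reverses under some plausible mixes, and every magnitude is assumed.

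A further objection is that a condensed article may leave covariates and strata to an analysis plan that is not shown, and multinomial regression could include starting category. That is fair for the regression. It does not reach the endpoint, whose denominator and two counted moves are set in the article itself, or the stated between-area contrast of that proportion.

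Finally, this is a non-randomised pilot, where baseline imbalance is a known limitation. True, but here the endpoint itself turns imbalance into an apparent effect, and stratifying would remove that component.

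**Conclusion.** The point holds as a structural weakness of the primary endpoint. As defined, it gives different proportions in areas with the same behaviour but different starting mixes, and the stated comparison does not condition on starting category. Unequal mixes are plausible here, with the wards likely, but not shown, to start less active.

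Size and sign cannot be determined from the article. Under the assumptions above, the false difference ranges from -0.75 points through near zero to +4.25 points, against a 10-point target; other assumed mixes and rates would give other values. If the starting mixes are equal, it is zero. The point concerns the upward-move endpoint only. The Research hypothesis and sample-size sections use a different quantity, the share active, which would need its own baseline comparison.

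**What to change.** In the Primary outcome measures and Data analysis sections:
1. Restrict the endpoint to participants below the recommended level at wave 1.
2. Compare areas within starting category (little or none; some).
3. Combine the two strata by a Mantel-Haenszel risk difference, or standardise the comparator to the wards' wave-1 mix.
4. Report the two transitions separately.

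Step 1 alone is not enough, as the remaining +1.8 points in the main case show.

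**Cost.** The change needs no data beyond what the endpoint already requires: starting and follow-up category for individuals in both areas. However, only ward respondents are described as being surveyed again at wave 2, and the article does not show that the Active People Survey gives both categories for the same people. The sponsor should confirm this first, because without it neither the stated endpoint nor the stratified comparison can be computed for the comparator.

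About 7.5% of ward respondents would leave the endpoint: 283 × 0.925 is about 262. Keeping 283 eligible would take about 283/0.925 = 306 respondents. The 10-point target would need restating for the new denominator, since 10 points among eligible ward residents equals 10 × 0.925 = 9.25 points among all ward participants. Bias from misreported starting category would remain.

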##### Secondary Outcome measures

These will include; proportion of the population eating 5 portions of fruit/vegetables a day, perceived health (SF-12), a sub-set of question items used by the Health Survey for England and recommended by the Office for National Statistics (ONS) will be used to assess social capital [25]. Aspects of social capital and social change will be explored in greater depth through focus group discussions on themes related to; social participation, civic partnership, social networks, reciprocity/trust and perception of local neighbourhood environment. We will triangulate qualitative findings from these focus groups with quantitative survey data.

### Assessment of processes

Qualitative data will be collected at various stages of the project. This will involve individual interviews and group discussions with selected residents. This will assess their perceptions of the programme and their integration of it into their everyday lives. These interviews will be conducted prior to the intervention, at least twice during the intervention, and after the intervention has concluded. The interviews will be tape-recorded and subjected to thematic analysis [30]. In addition, interviews will be conducted with a sample of the various social and health professionals and volunteers involved in the project to identify their perceptions of the programme and the challenges they had encountered in its implementations. Based upon previous comparable work it is intended that for each area 20 residents will be interviewed in one-to-one interviews and there will be 8 group discussions with approximately 6 residents in each group. This is a total of 68 residents together with 10 professionals and volunteers. Written, informed consent will be obtained from study participants. It is intended to supplement the interviews and discussions with substantial ethnographic field notes, narrative diaries (videos and photographs) and other data (e.g. photographs, minutes of meetings, newspaper reports, etc.) collected by the researchers on community meetings and other activities. This broad array of data will be collated and systematised to develop a sophisticated understanding of the processes involved in the development of the intervention [9].

### Data analysis

Chi-squared analysis will be used to test for differences in the distributions of PA categories in the intervention and control areas. Multinomial logistic regression analysis will be used to derive odds ratios for the various physical activity categories between the areas. Qualitative analysis of the interviews and discussion groups will follow the principles of thematic analysis [30]. The interviews will be audio tape-recorded, transcribed and entered onto a database. Then using the qualitative analysis computer package N-Vivo it is planned to conduct a thorough coding of the data followed by identification of basic themes and larger themes.

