### Study design

Case study pre-post test intervention in three electoral Ward areas of similar socio-economic deprivation [14] in a deprived inner city in the UK with an estimated population of ~10,000 adults.

Targeted communities in these wards will take part in an intensive community-led project, designed to engage its residents in the development and delivery of a range of health related interventions over a period of 2 years. The intervention will:

1. use community participatory research to build an effective community partnership in order to engage community residents, and strengthen community involvement and participation

2. use partnership consensus to identify, prioritise and design intervention(s) related to specific health disparities (and their relevant environmental determinants and mediators)

3. recruit local residents and Third Sector organisations to help with the delivery and sustainability of the target intervention(s)

4. establish local systems for ongoing monitoring and evaluation of the intervention

5. establish a local Public Health Advisory Group comprised of members from cross-government departments (e.g. urban planning, architecture, health, police and transport) to help facilitate policy change

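### The primary outcome is change in physical activity relative to the other wards, but the stated tests compare areas with no wave, baseline or change term, so an existing ward gap is mixed with the effect

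*Protocol article*

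**What the plan says.** - Design (Study design): "Case study pre-post test intervention in three electoral Ward areas of similar socio-economic deprivation". The community survey is sent again at 24 months to everyone who answered at wave 1 (Community survey).
- Choice of wards (Study population): they are "in the most deprived 40% of the 2007 Index of Deprivation" and "are not undergoing major housing regeneration over the next 3 years". The Abstract places them among the city's most deprived. No randomisation or matching to the comparator is described.
- Primary outcome (Primary outcome measures): "the change in physical activity in the three areas compared with the other wards in Stoke-on-Trent", with the Active People Survey named as the source. The same paragraph then gives a participant-level version, a 10% difference "in the proportion of participants reporting an increase in physical activity".
- Hypothesis (Research hypothesis): a different definition, the proportion active at moderate intensity on at least 3 days a week.
- Analysis (Data analysis): "Chi-squared analysis will be used to test for differences in the distributions of PA categories in the intervention and control areas". Then: "Multinomial logistic regression analysis will be used to derive odds ratios for the various physical activity categories between the areas". No other quantitative analysis of the primary outcome is stated.

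**The concern.** The outcome asks whether activity rose more in the three wards than elsewhere. The stated tests ask whether the areas differ. The two questions have the same answer only if the areas were equally active at the start.

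There is good reason not to assume that. The wards were picked for deprivation and the comparator is the rest of the city. The sample size section takes its 7.5% from a low socio-economic sub-group (NS-SEC 6-8) because that group best matches the target population, so the authors themselves treat activity as depending on socio-economic position. The Discussion links deprived areas with poorer access to places for activity and with sedentary behaviour.

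The Study aims section says the effect size will be used to design a larger controlled trial if findings are positive. An estimate mixed with a prior gap could stop that trial wrongly or give it the wrong size.

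**Working it through.** **Inputs from the protocol article (Proposed sample size).** Wards at baseline 7.5%; planned level after the intervention 17.5%; 283 participants at follow-up; error rate .05 (taken as two-sided); power .8.

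**Assumed, because the documents do not give them.** Proportion active in the other wards: 7.5%, 12.5% or 15%, unchanged over time. Comparator sample: 283 to 500. The outcome is reduced to active or not active. The multi-category test cannot be computed without category proportions.

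**The plan's own figure.** With φ = 2 arcsine(√p), φ(17.5%) = 0.8632 and φ(7.5%) = 0.5548, so h = 0.308, not the stated 0.273. At h = 0.308 the two-sided requirement at 80% power is 2(1.960 + 0.842)²/0.308² ≈ 165 per group; at h = 0.273 it is 211. So 283 does not reproduce at the stated inputs. That is a separate matter; 283 is used below as the planned number.

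**Follow-up comparison between areas.** Power ≈ Φ(|h|·k − 1.96), where k = √(283m/(283 + m)). This gives k = 11.90 for m = 283 and 13.44 for m = 500. φ(12.5%) = 0.7227 and φ(15%) = 0.7954.

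| Other wards | Planned effect (wards at 17.5%): h | Detected, m = 283 / 500 | No effect (wards at 7.5%): h | Rejected, m = 283 / 500 |
|---|---|---|---|---|
| 7.5% | 0.308 | 96% / 99% | 0 | 5% / 5% |
| 12.5% | 0.140 | 39% / 47% | −0.168 | 52% / 62% |
| 15% | 0.068 | 13% / 15% | −0.241 | 82% / 90% |

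Example, 12.5% with m = 283: 0.1405 × 11.90 = 1.67, and Φ(1.67 − 1.96) = 0.39. With no effect: 0.1679 × 11.90 = 2.00, and Φ(2.00 − 1.96) = 0.52. A negative h means the intervention wards look worse. At an assumed comparator of 17.5%, the planned gain would be wholly hidden: h = 0 and rejection is 5%.

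**Difference in change, 283 in each of four independent cells.** SE² = [0.075·0.925 + 0.175·0.825 + 2p(1 − p)]/283, with p the comparator level; power = Φ(0.10/SE − 1.96).

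| Other wards | Bracket | SE | 0.10/SE | Power |
|---|---|---|---|---|
| 7.5% | 0.3525 | 0.0353 | 2.83 | 81% |
| 12.5% | 0.4325 | 0.0391 | 2.56 | 73% |
| 15% | 0.4688 | 0.0407 | 2.46 | 69% |

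The four cells are treated as independent. Repeat respondents would alter these figures, but the documents give no within-person correlation.

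**The case against.** **The categories may be categories of change.** The participant-level outcome is built from moves up between activity levels. If the categories in the chi-squared test are those moves, the test does compare change and uses baseline. This is the strongest defence and cannot be ruled out. But the Data analysis section does not say so, and its reference to various physical activity categories reads more naturally as activity level. If change was meant, the section still has to say it.

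**A short article leaves model terms to a fuller document.** True of covariates and of the handling of repeat respondents; their absence is no fault here. The article does, however, name its tests, and as named they do not address its own primary outcome.

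**The size is assumed.** This stands. No comparator proportion or sample size is given, and the city as a whole is called deprived, so the gap could be small. With no gap the stated test works well.

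**A reader might infer that the plan is liable to produce a false benefit.** The documents do not support that. Every no-effect scenario with a gap makes the intervention wards look worse. A false benefit would need these wards to have begun more active than the rest of the city, and nothing in the article suggests it. Nor is the omnibus test's lack of direction a strong complaint, since the multinomial odds ratios would show direction.

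**Conclusion.** The stated primary outcome and the stated tests conflict, and following the Data analysis section as written can give a wrong answer about the intervention. The likely error is a masked benefit or an apparent harm.

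The size depends on a gap that the documents do not quantify. At an assumed comparator level 5 percentage points above the wards' baseline, power for the planned effect is below one half and the no-effect rejection rate is above one half. With no gap, neither problem arises. These figures describe a two-category comparison at follow-up and are illustrations, not predictions for this city. The conflict itself does not depend on them.

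**What to change.** - State first which activity definition is primary. The Research hypothesis (active on at least 3 days a week) and the Primary outcome measures (participants who increase) differ, and this is a choice of endpoint, not just of wording.
- For a proportion-active outcome, make the primary analysis a regression with area, wave and area-by-wave terms, using the Active People Survey before and after for the other wards. Test the interaction and report the difference in change in percentage points with a 95% CI.
- If the participant-level increase is kept as primary, say that the categories are categories of change, and confirm that the comparator source can supply them. The article describes repeat respondents only for its own survey.
- Allow for repeat respondents in the community survey. Adjust only for characteristics available in both sources; gender, age, ethnicity, education and tenure are shown for the community survey alone.
- Keep the chi-squared and multinomial analyses as descriptive.

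Cost: no new survey wave in the three wards, but lower precision than a single-time comparison. If the comparator were at 7.5%, power would drop from about 96% to about 81% with 283 per cell. To reach 80%, about 277 per area per wave are needed at a 7.5% comparator and about 339 at 12.5%. The stated power should be restated for this analysis.

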### Research hypothesis

It is predicted that a community-led intervention (working with the community and multiple agencies collectively to achieve beneficial change in a given factor) will increase the proportion of the target population who are physically active (taking part on at least 3 days/week in moderate intensity sport and active leisure) by 10% more (after a two year of intervention).

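### The named quantitative tests compare areas with no wave or baseline term, although the primary outcome is a difference in change and the sample size rests on a before/after rise

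*Protocol article*

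**What the plan says.** All references are to the protocol article.

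- **Study design:** "Case study pre-post test intervention in three electoral Ward areas of similar socio-economic deprivation".
- **Research hypothesis:** the programme "will increase the proportion of the target population who are physically active", by 10% after two years, where active means moderate-intensity activity on at least 3 days a week.
- **Proposed sample size:** from a starting value of 7.5%, "we anticipate being able to achieve a 10% increase in this population proportion i.e. 17.5% after the community-led intervention". The result is 283 participants at follow-up.
- **Community survey:** wave 1 respondents are approached again at 24 months. This is said to give enough power for the expected 10% difference, and weights for within-household selection are to be applied in the analysis.
- **Primary outcome measures:** the outcome "will be the change in physical activity in the three areas compared with the other wards in Stoke-on-Trent", with the Active People Survey as source. A second sentence, also about activity, begins "The study is designed to detect a 10% increase (intervention areas vs. the rest of Stoke-on-Trent) in the proportion of participants reporting an increase in" (cut short here), and builds that proportion from people classified by their initial activity.
- **Data analysis:** "Chi-squared analysis will be used to test for differences in the distributions of PA categories in the intervention and control areas". Then: "Multinomial logistic regression analysis will be used to derive odds ratios for the various physical activity categories between the areas". The rest of the section concerns qualitative data.

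**The concern.** The outcome, the hypothesis and the sample size all concern change over time. The two named tests have area as their only factor and mention neither wave nor baseline.

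The areas were not randomised. The three wards were chosen for deprivation and the comparator is the rest of the city, so equal starting levels cannot be presumed. A difference in levels between such areas is not the programme effect: a programme that does nothing can show a significant difference. The project aims to reduce inequalities, so one that lifts the wards to the city's level can show none. The Study aims section says that the effect size will be used to design a larger controlled trial, so an area gap taken for an effect would carry forward.

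**Working it through.** **1. Which contrast each section implies**

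| Section | Contrast |
|---|---|
| Study design, Research hypothesis, Proposed sample size | wave 2 minus wave 1, within the three wards |
| Primary outcome measures | change in the three wards minus change in the other wards |
| Data analysis | intervention areas versus control areas, no wave named |

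The third row equals the second only if the areas start at the same level.

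**2. The plan's own figure.** Cohen's h = |2 arcsin√0.075 − 2 arcsin√0.175| = |0.5548 − 0.8632| = 0.308; the article gives 0.273. With n per group = 2(z₁₋α/₂ + z_power)²/h², two-sided alpha 0.05 and power 0.80:

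- h = 0.308: 2(1.960 + 0.842)²/0.308² = 165.05, so 166.
- h = 0.273: 210.6, so 211.

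Neither reproduces 283. The closest match found is h = 0.273 with power 0.90, which gives 282 per group. This discrepancy is separate from the present point. What matters here is that the calculation compares 7.5% before with 17.5% after.

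**3. What a between-area test of levels would do**

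Inputs: intervention wards at 7.5% before and 17.5% after with full effect (Proposed sample size). Assumptions: 283 respondents per side (the article does not say whether 283 is per group or total, and gives no comparator sample size); a comparator rate that is the same at both times, varied from 7.5% to 17.5% because the article gives none; a two-sided arcsine test at 0.05.

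Rejection probability = Φ(d − 1.96) + Φ(−d − 1.96), with d = h√(283/2).

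At a comparator rate of 12.5%:

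- No effect, 7.5% versus 12.5%: h = 0.168, d = 1.998, rejection 0.515.
- Full effect, 17.5% versus 12.5%: h = 0.140, d = 1.671, rejection 0.386.

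| Comparator, flat at | Rejection, no effect | Difference seen with full effect | Rejection, full effect |
|---|---|---|---|
| 7.5% | 5% | 10 points | 96% |
| 10% | 18% | 7.5 points | 74% |
| 12.5% | 52% | 5 points | 39% |
| 15% | 82% | 2.5 points | 13% |
| 17.5% | 96% | 0 points | 5% |

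**4. Precision of a change contrast.** Comparator 12.5%, full effect, 283 per cell, independent cells:

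- Follow-up levels only: √[(0.1444 + 0.1094)/283] = 0.030.
- Difference in change: √[(0.1444 + 0.0694 + 0.1094 + 0.1094)/283] = 0.039.

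Power for a 10-point difference in change is then Φ(0.10/0.0391 − 1.96) = 0.73, against 0.39 for the comparison of levels.

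**The case against.** A reader might infer that no before/after comparison is planned anywhere and that the effect will never be estimated. The documents do not support that. The Community survey section re-surveys wave 1 respondents, ties this to power for the expected 10% difference and provides analysis weights. A contrast over time is clearly intended; what is absent is a named test for it.

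It is also fair to say that the Data analysis section does not limit itself to follow-up data, and that an article commonly leaves model terms to a fuller document. But the section does fix two tests and their grouping factor, and as stated they do not match the article's own primary outcome. That is a conflict in the text rather than missing detail.

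The strongest defence is that the activity categories are the change groups described under Primary outcome measures. A chi-squared test by area would then compare change. The Data analysis wording does not say this. That reading would also need the same individuals followed in the comparator wards, and the article describes repeat surveying only in the study areas. Even then, the rise used for the sample size would have no named test.

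Finally, the error rates depend on assumed comparator rates and on 283 per side. That objection stands: the figures show how such a test could mislead, not how far it would mislead in Stoke-on-Trent.

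**Conclusion.** The point holds as a mismatch between the stated tests and the stated outcome. The two named tests compare areas without wave or baseline, while the primary outcome is a difference in change and the sample size concerns a rise within the wards. As written, the tests would confound an existing area difference with the programme effect.

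The mismatch itself depends on no assumed number. Its size does: with a comparator flat at 12.5% and 283 per side, rejection is about 52% under no effect and 39% under the full effect. With equal starting levels it would be 5% and 96%, and the problem would largely vanish. The 52% should not be read as this study's false-positive rate, because the article gives no activity rate for the rest of the city.

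**What to change.** In the Data analysis section:

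1. Make the primary analysis an area by wave contrast on the proportion active, as defined in the Research hypothesis and Proposed sample size sections. Use both waves of the community survey with the selection weights, allow for repeated respondents, and take the Active People Survey rounds nearest each wave for the rest of Stoke-on-Trent.
2. Report the weighted wave 1 to wave 2 change within the three wards as the contrast used for the sample size.
3. State under Primary outcome measures that the proportion active replaces the proportion reporting an increase for the between-area comparison, because the article provides no followed individuals in the comparator wards. This changes the endpoint wording and should be declared as such.
4. State the fallback: if matching survey rounds are not usable, the within-ward change is the primary result and between-area comparisons are descriptive.

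**Cost.** The community survey needs no new fieldwork, but someone must check that the Active People Survey has rounds near both waves with usable Stoke-on-Trent samples and compatible items; the article does not establish this. The interval widens: the standard error is about 3.9 points instead of 3.0 under the assumptions above with independent cells, and less if repeated respondents' answers are positively correlated.
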